# “More air—better performance—faster recovery”: study protocol for randomised controlled trial of the effect of post-stroke inspiratory muscle training for adults

**DOI:** 10.1186/s13063-021-05551-8

**Published:** 2021-08-28

**Keywords:** Inspiratory muscle training, Fatigue, Stroke, Endurance in gait, Voice volume and phonation, Activity of daily living, Spirometry, Peak expiratory flow

## Abstract

**Background:**

Stroke results in varying physical, cognitive, emotional and/or social disabilities in the short and long term alike. Motor impairments are important, persistent consequences of stroke and include, among others, decreased respiratory muscle function, decreased ability to expand the thorax and postural dysfunction. These deficits affect the patient’s ability to perform daily activities, produce fatigue and reduce endurance and quality of life. Inspiratory muscle training (IMT) aims to improve the strength and endurance of the diaphragm and the external intercostal muscles. The objectives of this study are to investigate the effect of 3 weeks of IMT on (i) maximal inspiratory pressure (MIP) in adults having suffered a stroke, as well as (ii) functional activities and expiratory measurements.

**Methods/design:**

This is a randomised controlled trial (RCT) comparing IMT with conventional neurorehabilitation (usual practice). The trial will include 80 patients with reduced MIP hospitalised at a specialised neurorehabilitation hospital in Denmark. The intervention group will receive IMT sessions, exercising at 30% of MIP. Patients in the intervention group will perform two daily sessions (one session of IMT with Threshold IMT consisting of two times 15 inspirations at normal breathing rhythm (5–10 min)), 7 days a week for 3 weeks. Training can be with or without physiotherapist supervision. Study outcomes: MIP assessed by the Power Breath, Functional Independence Measurement, The 6-min walk test, the Fatigue Severity Scale and average voice volume. Expiratory function will be assessed using spirometry. All assessments will be conducted at baseline and 3 weeks (at termination of the intervention) and 3 months after the intervention has concluded.

**Discussion:**

IMT is a promising and partly self-managed tool for rehabilitation to improve respiratory function. The introduction of IMT in combination with traditional physical therapy may enhance faster recovery after stroke and may at the same time demand little personnel resources to increase training intensity. This trial will provide further evidence of IMT to clinicians, patients and health managers. Hereby, this study accepts the call for further research.

**Trial registration:**

ClinicalTrials.govNCT04686019. Registered on 28 December 2020.

**Supplementary Information:**

The online version contains supplementary material available at 10.1186/s13063-021-05551-8.

## Background

In Denmark (counting approximately 5.8 million inhabitants [1]), 12,500 people experience stroke annually [2]. The incidence is highest in the elder part of the population. As the average life expectancy increases, stroke is expected to become an even heavier burden on the healthcare system [2, 3]. Stroke results in varying physical, cognitive, emotional and/or social disabilities in the short and long term alike [4, 5]. Motor impairments are significant and persistent consequences of stroke and include decreased respiratory muscle function, decreased ability to expand the thorax and postural dysfunction, among others [6–9]. These deficits affect the patient’s ability to engage in daily activities, produce fatigue, reduce endurance and affect quality of life.

Inspiratory muscle training (IMT) aims to improve the strength and endurance of the diaphragm and external intercostal muscles [9]. In sports, IMT serves to improve athletes’ respiratory capacity [10, 11]. Smaller studies have tested the method in post-stroke patients, and results indicate that IMT has a positive effect on respiratory muscle function, exercise capacity and quality of life [12–14]. A review recommends using IMT as an intervention for patients suffering from chronic obstructive pulmonary disease (COPD) [15]. In Denmark, IMT has been applied in practice, for instance in persons with tetraplegia in the acute phase. IMT has also been used in treatment of people with COVID-19; however, knowledge of the use of IMT is surprisingly sparse. This project will be one of the first to bridge this knowledge gap. Clinical experiences in neurorehabilitation imply that IMT may improve voice volume, phonation endurance and coughing force (airway clearance). It would be useful to substantiate evidence presented for this hypothesis. It is therefore relevant to test the intervention in a larger study setup.

The aim of this trial is to determine the efficacy of a three weeks IMT intervention in adults post-stroke.

### Objectives

The two primary objectives of this study are to investigate:
The effect of 3 weeks of IMT on maximal inspiratory pressure (MIP) in adults having suffered stroke.The effects of 3 weeks of IMT on the degree of dependency in activities of daily living, endurance in gait, fatigue, voice volume (VV), phonation endurance (PE) and expiratory function; peak expiratory flow (PEF), forced expiratory volume in 1 second (FEV1), forced vital capacity (FVC) and FEV1/FVC ratio.

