### Outcomes

The primary outcome measure is MIP assessed by Power Breath [18]. This is an objective measurement used to describe the inspiratory capacity.

Secondary outcome measures include the following: the Functional Independence Measure (FIM) to assess the degree of dependency in daily activities—both total score and motor sub score [19]—and the 6-min walking test to measure endurance [20–22]. Fatigue was measured by the Fatigue Severity Scale [23, 24]. Average voice volume will be measured by recording of an a-sound with the app Voice Analyst. Phonation endurance (how long the a-sound lasts) is noted. The patient tries three times, and the average is then calculated. Expiratory function is as follows: peak expiratory flow (PEF), forced expiratory volume in 1 s (FEV1), forced vital capacity (FVC) and FEV1/FVC ratio will be assessed with Spirometry device (Vitalograph Micro 6300, Ireland). All respiratory measures are performed in sitting position. The patient tries three times. Subsequently, the best score is used for further analysis [12].

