### Statistical analysis

Data will be analysed as intention-to-treat and per protocol. Between-group differences (3-month follow-up minus baseline) are compared by the *T* test. Regression analysis is conducted with adjustment for the confounders’ age and time from stroke to baseline assessment.

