## Discussion

The primary purpose of this study is to assess the effect of an IMT intervention in patients with reduced MIP following stroke. A secondary purpose is to assess the effect of IMT on the degree of dependency in activities of daily living, endurance in gait, fatigue, voice volume, phonation endurance and expiratory capacity. Hereby, this study accepts the call for further research made by Xiao [9].

The study assumes that by strengthening the diaphragm muscle and the intercostal muscles, patients will gain faster respiratory recovery, which, in turn, will allow them to practice or carry out activities of daily living earlier in the course of their rehabilitation. The typical length of IMT interventions is 6–8 weeks [12, 13, 26]. In 2019, the average hospitalisation in the study setting for stroke patients was 34 days (95% CI 21–52 days). The length of the intervention was set to 21 days to ensure that the intervention could be completed during hospitalisation. The duration of the intervention was also informed by positive results from the pre-study. We argue that it is interesting to investigate whether or not a shorter intervention period is sufficient for patients to experience a positive impact on MIP and the degree of their dependency in activities of daily living, endurance in gait, fatigue, voice volume, phonation endurance and expiratory function*.* Especially, we find it valuable to investigate the effect of increasing intensity in rehabilitation as the intervention is relatively easy and inexpensive to implement and may be practiced by many patients on their own as an add-on to their rehabilitation.

A broad spectrum of patients with sensorimotor deficits following stroke is expected to be included in the study, as it does not exclude patients based on the severity of their stroke. We find it important to develop interventions that may also have an impact on the more severely injured patients.

Sham IMT was considered for the control group, but was rejected for ethical reasons, as it would be time consuming for patients to do the sham intervention, which would be unethical as these patients need to economise their resources due to fatigue.

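### The Objectives section ranks ten outcomes as primary, while Outcomes, Sample size and Discussion rest on MIP alone, and no single MIP analysis is named to carry the conclusion

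*Protocol article*

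**What the plan says.** The Objectives section introduces its list with "The two primary objectives of this study are to investigate". The first item is "The effect of 3 weeks of IMT on maximal inspiratory pressure (MIP) in adults having suffered stroke". The second item covers "the degree of dependency in activities of daily living, endurance in gait, fatigue, voice volume (VV), phonation endurance (PE) and expiratory function", with expiratory function spelled out as "peak expiratory flow (PEF), forced expiratory volume in 1 second (FEV1), forced vital capacity (FVC) and FEV1/FVC ratio". Nothing in that section ranks one item above the other.

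The Outcomes section is different: "The primary outcome measure is MIP assessed by Power Breath", and the remaining measures are introduced as secondary. The Discussion agrees with the Outcomes section. It gives MIP as the primary purpose and continues: "A secondary purpose is to assess the effect of IMT on the degree of dependency in activities of daily living", followed by the rest of the same set. The Sample size section defines its quantity as change in MIP from baseline to 3 months, with 5 cmH2O as the smallest relevant difference, and mentions no other outcome.

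On analysis the article says "Data will be analysed as intention-to-treat and per protocol". It then names a T test on the change to 3 months and a regression adjusted for age and time from stroke to baseline. Baseline MIP is not among the covariates, and no order is given for the populations or the methods.

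**The concern.** The word primary settles which result the trial stands or falls on. Under the Objectives section, a favourable result on fatigue, voice volume or FEV1 could be reported as meeting a primary objective even if MIP showed nothing. Under the Outcomes section it could not. The article supports both readings. The Abstract does not resolve the matter: it joins MIP and the functional and expiratory measures in one statement of objectives, and lists the study outcomes without ranking them.

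The second part is narrower. Even with MIP as the only primary outcome, two populations and two methods yield four results for it, and the article does not say which one is the answer. The regression also leaves out baseline MIP, which every patient will have because reduced MIP is an entry criterion and MIP is measured at baseline.

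**Working it through.** **1. Sections side by side**

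| Section | Status of MIP | Status of the other outcomes |
|---|---|---|
| Objectives | primary | primary |
| Outcomes | primary | secondary |
| Sample size | the only outcome used | not used |
| Discussion | primary purpose | secondary purpose |

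Three sections point to MIP alone. One does not.

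**2. Counting the outcomes in Objectives**

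- Objective 1: MIP = 1.
- Objective 2: dependency in daily activities, gait endurance, fatigue, voice volume, phonation endurance = 5; PEF, FEV1, FVC, FEV1/FVC = 4. Together 9.
- Total: 1 + 9 = 10.

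**3. What the trial was sized for**

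The stated figure is 60 intervention and 20 control patients. It cannot be fully reproduced, because significance level, power and absolute SDs are not given. Two features can be checked:

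- The most efficient split is in proportion to the SDs. The assumed SD ratio is 3, and 60/20 = 3.
- With 10% dropout, 18/0.9 = 20 and 54/0.9 = 60.

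Solving backwards for the control SD s, at an assumed two-sided 5%, uses s = 5 / [(z for alpha + z for power) × √(1/18 + 9/54)], where the square root is 0.471:

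- 80% power: s ≈ 3.8, so 11.4 in the intervention arm.
- 90% power: s ≈ 3.3, so 9.8 in the intervention arm.

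Every input is a MIP quantity. Nothing in the calculation covers the nine outcomes of objective 2.

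**4. False-positive chance if Objectives were taken literally**

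With k independent tests at 5% each and no true effects, the chance of at least one false positive is 1 − 0.95^k.

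- k = 1: 0.05.
- k = 10: 1 − 0.95^10 = 0.401.

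The 5% is an assumption. The outcomes are related (FEV1/FVC is computed from two others on the list), so the true figure would be below 0.401.

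**5. Four analyses of MIP**

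2 populations × 2 methods = 4. If independent, 1 − 0.95^4 = 0.185. They share most of their data, so a null simulation (4,000 runs) is more informative. It assumed 18 and 54 patients analysed, SD ratio 3, covariates explaining about 20% of the variance, 80% of the intervention arm kept at random in the per-protocol set, and methods that allow unequal variances. Each analysis rejected in 4.5% to 5.1% of runs, and at least one of the four in about 10%.

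**6. Why the standard errors matter**

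Take 18 and 54 patients with SDs s and 3s.

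- Correct standard error: s√(1/18 + 9/54) = 0.471s.
- Pooled variance: (17 × 1 + 53 × 9)/70 = 7.06 s². Pooled standard error: s√[7.06 × (1/18 + 1/54)] = 0.723s.
- Ratio: 0.723/0.471 ≈ 1.53.

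If the planning assumption holds, an analysis that pools the variances would overstate the standard error by about half and lose the power the unequal split was meant to secure.

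**The case against.** The best reply is that this is a slip of one word. Outcomes, Sample size and Discussion all settle on MIP, so a fair reader knows what is primary. The 40% describes a practice nobody has proposed. Ranking populations and methods is also ordinary content for an analysis plan, which may exist unseen.

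Much of this stands. The weight of the article favours MIP, and the 40% is a ceiling for a literal reading, not a forecast. The lack of a ranking would not be a finding by itself. What remains is that an analysis plan would not correct a published Objectives section that conflicts with the published Outcomes section.

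Four stronger readings are tempting and are not supported:

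- **Eleven primary outcomes, 43%.** Eleven requires counting FIM twice ("both total score and motor sub score"). That split appears only in the Outcomes section, which makes FIM secondary.
- **A stated 5% error rate is broken.** The article states no significance level.
- **Four analyses of MIP contradict a single primary outcome.** They do not; one outcome can be analysed several ways. The question is only which analysis leads.
- **A per-protocol result restricted to patients who trained as prescribed could displace the randomised comparison.** Only the intervention arm keeps a training log, but the article does not define the per-protocol set or say that the log determines it. The restriction is conjecture.

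**Conclusion.** The contradiction over objective 2 is real and bears on which results may be claimed as primary. Nine outcomes are primary in Objectives and secondary in Outcomes and Discussion, and they play no part in the sample size. If all ten outcomes were tested as primary, the chance of at least one false positive would be at most about 40%. That assumes 5% per test, no correction, independence and no true effects; correlation lowers it.

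The open choice among MIP analyses is a lesser point that an unseen analysis plan may settle. Its illustrative size is about 10% instead of 5%, under the simulation assumptions, if any of the four results could be taken as the answer. It is worth closing in the same edit, because baseline MIP is already collected but absent from the covariates, and because the assumed threefold SD ratio makes the choice of standard error consequential. The precision gained from baseline adjustment cannot be computed, since the article gives no correlation between baseline and 3-month MIP.

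**What to change.** - **Objectives:** keep MIP as the one primary objective and relabel the second as secondary, to match Outcomes, Sample size and Discussion.
- **Statistical analysis:** name one primary analysis: intention-to-treat, MIP at 3 months, by regression with baseline MIP added to age and time from stroke, and standard errors that allow the unequal variances assumed in Sample size. With baseline MIP in the model, the treatment estimate is the same whether the response is the 3-month value or the change, so the planned quantity is kept.
- **Supporting analyses:** report the per-protocol analysis and the unadjusted T test under that label.

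The cost is two edits to the text and one covariate that is already measured. Sample size, data collection and conduct do not change. The adjusted regression would lead in place of the unadjusted T test, so the change should be made and dated before outcome data are examined by arm. The small downside is that objective 2 results can no longer be presented as meeting a primary objective.

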## Methods/design

### Design

This study is a randomised controlled trial (RCT) comparing IMT with conventional neurorehabilitation (usual practice). Baseline assessments are made 0–4 days before the intervention starts. Further assessments are performed 0–4 days after the intervention concludes and at the 3-month follow-up. Assessments will be conducted by assessors blinded to the randomisation and the intervention.

### Patient population

We plan to enrol 80 patients in the study. All patients will be recruited from a specialised neurorehabilitation hospital in Denmark.

### Inclusion criteria

First-time brain infarction or brain haemorrhage within the past 0–3 monthsAge > 17 yearsAble to give written consent and being cognitively and communicatively able to understand and participate in the MIP testReduced MIP below the gender- and age-specific normal standard given in Table 1. Patients > 74 years of age will be categorised as having reduced MIP according to the subgroup age 70–74 standard values.

**Table 1 Tab1:** MIP—gender- and age-specific standard

Standard values for maximal inspiratory pressure (MIP)					
Age	20–54	55–59	60–64	65–69	70–74
Men	124 ± 44	103 ± 32	103 ± 32	103 ± 32	103 ± 32
Women	87 ± 32	77 ± 26	73 ± 26	70 ± 26	65 ± 26

### Exclusion criteria

Patients with the following characteristics will be excluded: diagnosis of myocardial infarction within the past 3months, significant pulmonary disease (severe COPD), saturation below 90 if having COPD and for others a saturation below 92, neurological deficits other than stroke, facial palsy affecting proper labial occlusion and dizziness or nausea/vomiting during MIP testing (Fig. 1).

**Fig. 1 Fig1:**
[figure not shown]
Patient flowchart

### Randomisation

An independently controlled, computer generated randomisation will be implemented in REDCap [16, 17] by an externally based datamanager. The allocation will be concealed to the involved assessors. Only the project management has access to the randomisation information in REDCap and only after each patient has been randomised. The project manager informs the physiotherapist at the ward about the allocation. Afterwards, the physiotherapist informs the patient. A stratified block randomisation of severity of impairment based on Modified Rankin Scale (mRS) (< 4) and a block size of 4 with an intervention/control ratio of 1/3 will be performed. Furthermore, a stratification on the two participating neurorehabilitation units will be performed.

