### Test procedure

All assessments will be conducted at baseline, 3 weeks (at termination of the intervention) and 3 months after the intervention concluded. The Patient Global Impression of Change (PGIC) scale will be employed upon conclusion of the intervention [25].

Outcome assessors are blinded to the intervention. Testing takes place in a specific room at the recruitment hospital. Outcome assessors are physiotherapists trained in performing the test procedures and are not joining the treatment team at the recruiting ward. Patients will be tested by the same therapist all three times. The trial participants and intervention providers are not blinded.

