### Sample size

Power was calculated to establish the needed number of participants. The power calculation was based partly on a local pre-study (including 26 patients) and on a RCT study [12], which showed differences in variance in ∆MIP assessments. ∆MIP is defined as (MIP at 3 months minus MIP at baseline). Because of the difference in variances in the intervention group and the control group, the same power can be achieved by distributing them unequally between the groups. It is assumed that the standard deviation is three times larger in the intervention group than in the control group. The power calculation prescribes 20 patients in the control group and 60 patients in the intervention group. Calculations were made, expecting a 10% dropout. The least clinically relevant difference was estimated to 5 cmH_2_O.

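### A single disclosed block size of 4 at a 3:1 split lets a fully informed tracker foresee about 44% of allocations; this weakens allocation concealment but does not defeat it

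*Protocol article*

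**What the plan says.** All references are to the protocol article.

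- **Randomisation** sets "a block size of 4 with an intervention/control ratio of 1/3", stratified by mRS with a cut at 4 and by the two participating units. An external data manager sets up the computer-generated list in REDCap.
- The same section states that "Only the project management has access to the randomisation information in REDCap and only after each patient has been randomised", and then that "The project manager informs the physiotherapist at the ward about the allocation"; the physiotherapist tells the patient. It states concealment only with respect to the assessors.
- **Test procedure** says that "The trial participants and intervention providers are not blinded". Assessors are blinded and work outside the ward's treatment team.
- **Data Availability** gives the researchers access to the REDCap database during data collection but keeps randomisation information from the assessors.
- **Sample size** says that "The power calculation prescribes 20 patients in the control group and 60 patients in the intervention group". This is 3:1 in favour of intervention, whereas the Randomisation section prints "intervention/control ratio of 1/3", which read literally is the reverse.
- **Trial status** has enrolment starting on 1 February 2021, with recruitment, follow-up and analysis complete by the end of December 2022. The article appeared on 28 August 2021, within that period.

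**The concern.** A 3:1 block of four contains exactly one patient in the smaller arm. Once that patient has appeared, the rest of the block is fixed; if the first three patients are all in the larger arm, the fourth is fixed. With one block size, stated in print, anyone holding the history of a stratum can work this out. Releasing each allocation only after it is made protects the current patient's assignment but supplies what is needed to predict the next one.

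If a person with that knowledge also influences who is approached, or when, the arms could come to differ in prognosis or motivation. There is some room for this: eligibility runs for up to three months after stroke and involves a judgement that the patient can understand and take part in the maximal inspiratory pressure (MIP) test. The primary outcome depends on effort, and with about 20 controls a few displaced patients could matter.

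**Working it through.** The article gives no predictability figure, so there is none to reproduce.

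**Inputs.** Block size 4 and strata by unit and mRS (Randomisation); 60 intervention and 20 control, hence 3:1 (Sample size). Assumption: the two factors are crossed, giving 2 × 2 = 4 strata. An allocation counts as known when the earlier ones in its block leave only one possibility.

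**Complete blocks of 4 at 3:1.** The smaller-arm patient is equally likely to be in each position.

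| Position of smaller-arm patient | Allocations known in advance |
|---|---|
| 1 | 3 |
| 2 | 2 |
| 3 | 1 |
| 4 | 1 |

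Mean = (3 + 2 + 1 + 1)/4 = 1.75 per block; 1.75/4 = 43.75%.

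By arm: the first three rows give larger-arm allocations, (3 + 2 + 1)/4 = 1.5 per block. The last row gives a smaller-arm allocation, 1/4 = 0.25 per block. Over 80/4 = 20 complete blocks, that is 20 × 1.5 = 30 of 60 larger-arm and 20 × 0.25 = 5 of 20 smaller-arm allocations.

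The total is the same if the printed ratio is taken literally as one intervention to three control; only the arm labels swap. A 2:2 block of four gives 33.3%, so the unequal split makes prediction easier.

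**80 patients with incomplete last blocks.** Simulation over four strata gave 41.7% for each of three assumed distributions of patients: 25/25/25/25, 40/10/40/10 and 50/30/15/5 per cent.

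**Tracking the unit without mRS.** Each unit contains two interleaved block sequences. A fully rational observer who knows the scheme and the unit's sequence, but not mRS level, was simulated over 40 patients per unit. The share known with certainty was 5.8%, 5.6% and 5.1% for assumed mRS splits of 50:50, 70:30 and 90:10.

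**Best-guess accuracy in blocks of 4.** A full tracker is right with probability 3/4 at each of positions 1 to 3 and with certainty at position 4: (0.75 + 0.75 + 0.75 + 1)/4 = 81.25%. Always guessing the larger arm, with no tracking, is right 75% of the time.

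**Alternative block sizes.** For a block with *a* patients in one arm and *b* in the other, the expected number known is a/(b + 1) + b/(a + 1).

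- 3 and 1: 3/2 + 1/4 = 1.75, or 43.75% (agrees with the table).
- 6 and 2: 6/3 + 2/7 = 2.286; 2.286/8 = 28.6%.
- Sizes 4 and 8 equally likely, tracker told each size: (1.75 + 2.286)/(4 + 8) = 33.6%. This is an upper limit; hidden sizes give less.

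**The case against.** A reader might infer that anyone on the ward can read off 44% of allocations and that concealment is therefore defeated. The article does not support that.

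- **The stratum is unit by mRS, not unit.** The 44% needs mRS level and every earlier allocation in that cell. The article says only that the ward physiotherapist is told an allocation, not that any one physiotherapist learns all of them. Without mRS the figure is about 5–6%. This stands, and it limits the finding to project management and, conditionally, ward physiotherapists.
- **More than half stays uncertain.** About 56% of allocations are undetermined even for a full tracker. Most of the known ones only confirm the likelier arm; certainty of a coming smaller-arm allocation arises for 0.25/4 = 6.25% of patients, about 5 of 80. On best-guess accuracy, full tracking adds 6.25 percentage points to the 75% baseline, and a block of 8 would still give 79.0%. This stands and argues for a modest rating.
- **The route to bias is not documented.** The article does not say who screens or enrols, or that those people know earlier allocations. Steering is possible in principle but not shown.
- **A leak to assessors is not shown either.** They are outside the treatment team and have no access to randomisation information. Any leak after allocation would be an unblinding problem whatever the block size.
- **The block size is already public.** Removing it from site documents would therefore achieve little. This is fair, but it does not touch a new list whose sizes are not disclosed.

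None of this answers the central point: access after each randomisation does not stop project management from deriving later allocations in the same block.

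**Conclusion.** The concern holds as a weakness of allocation concealment. With one disclosed block size of 4 at the implied 3:1 split, a person with the full history of a unit-by-mRS stratum knows 43.75% of allocations in advance in complete blocks, and about 42% across 80 patients.

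Project management is in that position on the article's own account: it sees the randomisation information after each patient, and the researchers have access to the database. Ward physiotherapists are in that position only if they learn all allocations in the stratum and know mRS level.

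The figures assume crossed strata and a tracker who knows the scheme; the unit-only figure also rests on the assumed mRS splits. The article does not establish that enrolment was steered, that assessors learned allocations or that concealment failed. The change is worth making because it is cheap and keeps the design, not because bias has been demonstrated.

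**What to change.** 1. Reconcile the printed "intervention/control ratio of 1/3" with the 60 intervention and 20 control patients in the Sample size section before any new list is generated.
2. For patients still to be randomised, have the external data manager generate randomly varying blocks of 4 and 8, each at the planned ratio, within the same unit-by-mRS strata.
3. Withhold the block sizes and their order from project management and site staff. State in the protocol that sizes vary, without giving them.

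With the two sizes equally likely, the share known falls from 43.75% to at most 33.6% even if every size were known, and lower if the sizes are hidden. The ratio and the stratification factors are unchanged.

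The cost is a new allocation list during recruitment and final arm totals that may depart slightly more from 60/20. The change helps only patients not yet randomised.

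### The stated intervention/control ratio of 1/3 reverses the 60 intervention and 20 control patients that the sample size prescribes; implemented literally, it makes the standard error 53% larger than planned

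*Protocol article*

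**What the plan says.** The Randomisation section of the protocol article describes stratified block randomisation, set up in REDCap by an external data manager, with "a block size of 4 with an intervention/control ratio of 1/3 will be performed". Strata are formed by mRS (below 4 or not) and by the two participating units.

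The Patient population section gives the total: "We plan to enrol 80 patients in the study". The Sample size section divides it: "The power calculation prescribes 20 patients in the control group and 60 patients in the intervention group". Its reason is variance: "Because of the difference in variances in the intervention group and the control group, the same power can be achieved by distributing them unequally between" arms. On the size of that imbalance it says: "It is assumed that the standard deviation is three times larger in the intervention group than in the control group".

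The same section adds "The least clinically relevant difference was estimated to 5 cmH_2_O" and "Calculations were made, expecting a 10% dropout". The Statistical analysis section says "Between-group differences (3-month follow-up minus baseline) are compared by the" T test, without naming the equal- or unequal-variance version.

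**The concern.** The two sections give opposite ratios for the same trial. With a block size of 4, a ratio of 1/3 can only mean one patient plus three, and the sentence names intervention first. Over 80 patients that is 20 intervention and 60 control, the mirror image of the Sample size section.

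The direction matters because the unequal split has a purpose. The design puts more patients in the arm expected to be more variable. Reversed, it puts the fewest patients there and is less precise than simple 1:1 allocation.

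The ratio in the Randomisation section is also the kind of figure from which an allocation table is programmed. Enrolment was due to start on 1 February 2021, and the current protocol version is dated 16 August 2021. If a reversed table was in use, patients may already have been allocated by it.

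**Working it through.** **Inputs from the protocol article.** Total 80 (Patient population). Split 60 intervention, 20 control; SD ratio 3; difference 5 cmH2O; dropout 10% (Sample size). Block size 4 and ratio 1/3 (Randomisation). T test on change from baseline to 3 months (Statistical analysis).

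**Not given, so assumed.** Two-sided alpha 0.05 and target power of 80% to 95%. One-sided 0.05 and two-sided 0.01 were also tried. Absolute SDs are not given, so results are in units of the control SD, s.

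**Step 1: the plan's own split.** For a fixed total, the variance of a difference in means is smallest when n_I/n_C = SD_I/SD_C = 3. For 80 patients this gives 80 × 3/4 = 60 intervention and 80 × 1/4 = 20 control, exactly the stated split. After 10% dropout, 72 patients divide as 54 and 18. The total of 80 cannot be reproduced without alpha, power and an absolute SD.

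**Step 2: precision under each ratio.** Var = (3s)²/n_I + s²/n_C.

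| Intervention/control | Variance (s²) | SE (s) |
|---|---|---|
| 60/20 (Sample size section) | 9/60 + 1/20 = 0.200 | 0.447 |
| 40/40 (for comparison) | 9/40 + 1/40 = 0.250 | 0.500 |
| 20/60 (Randomisation section, literally) | 9/20 + 1/60 = 0.467 | 0.683 |

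The SE ratio is 0.683/0.447 = 1.53. The variance ratio is 0.467/0.200 = 2.33, so a 1:3 design needs 80 × 2.33 ≈ 187 patients for the planned precision. This step uses only figures in the article. Equal 10% dropout in both arms leaves the ratios unchanged.

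**Step 3: power with an unequal-variance test.** Set the standardised effect so that 60/20 has the assumed power, then recompute at 20/60. By the normal approximation, power = Φ[(z for alpha + z for power)/1.53 − z for alpha]. For 80%: (1.960 + 0.842)/1.5275 − 1.960 = −0.126, and Φ(−0.126) = 0.45.

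| Assumed power at 60/20 (two-sided 0.05) | At 20/60, normal approximation | At 20/60, Welch t |
|---|---|---|
| 80% | 45% | 42% |
| 85% | 50% | – |
| 90% | 56% | 53% |
| 95% | about 65% | – |

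Across the other alphas, the share of planned power retained runs from about 46% (two-sided 0.01, 80% design: 36.7%) to about 73% (one-sided 0.05, 95% design: 69.5%).

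**Step 4: the version of the t test.** Simulation with SD ratio 3, nominal two-sided 0.05, 60,000 runs per setting, and the effect set for 80% power at 60/20 by the normal approximation:

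| Test | Type I error 60/20 | Type I error 20/60 | Rejection under the effect 60/20 | Rejection under the effect 20/60 |
|---|---|---|---|---|
| Unequal variance (Welch) | 4.9% | 5.1% | 79% | 41% |
| Pooled variance | 0.3% | 20% | 41% | 71% |

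Under the pooled test the literal ratio does not lower the rejection rate. It breaks the type I error.

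**The case against.** The strongest reply is that this is a transposed pair of figures and nothing more. The Sample size section gives explicit counts per arm and a reason that fits only those counts, so the intended design is clear and the data manager may well have programmed it. The patient flowchart and the additional files are not available here and may show the right ratio. This stands as far as harm is concerned: the article does not show which table is in REDCap. It does not remove the contradiction, since nothing in the available text reconciles the two statements.

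A reader might go further and infer that the trial has been randomised the wrong way round, or that its power is roughly halved. The article supports neither. It says nothing about the loaded table. Halving is close only for an assumed 80% design with an unequal-variance test; from 90% the relative loss is about 40%, and from 95% under a third. With a pooled-variance test the damage is excess false positives, not lost power.

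It is also fair to object that no sum in the protocol is wrong: 20 + 60 = 80, and 3:1 agrees with the stated SD ratio. This is a contradiction between two sections, not an arithmetic error.

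**Conclusion.** The point holds as an internal contradiction on a basic design feature, and it must be corrected. The article's own variance assumption identifies the Randomisation sentence as the wrong one.

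The contradiction is certain from the text. The size of the possible harm, an SE 53% larger than planned, rests only on the stated SD ratio and group sizes, and applies only if the ratio was implemented literally. Any figure for power or type I error also needs the unstated alpha, target power and t-test version, and should be quoted with those assumptions attached. Neither version of the test makes the literal ratio harmless.

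**What to change.** Change the Randomisation sentence to read: intervention:control 3:1, each block of four containing three intervention and one control. Have the external data manager confirm the ratio actually loaded in REDCap in each of the four mRS-by-unit strata.

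- **If the table is already 3:1:** the wording correction is enough. It costs one sentence and one check, and no patients.
- **If it was loaded as 1:3:** correct it for the remaining patients and record the date. Adjust the analysis for allocation period, because the change ties allocation to calendar time. Use an unequal-variance test, and restate the precision and power still achievable.

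In the second case moving to 3:1 does not recover 60/20 within 80 patients. As an illustration, suppose the switch comes after patient 40: 10/30 followed by 30/10 gives 40/40. The variance is then 0.250 s² instead of 0.200 s², and about 80 × 0.250/0.200 = 100 patients would be needed for the planned precision, before any cost of the period adjustment. The sponsor would have to choose between more patients and a stated loss of precision.
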